## Abstract

**Supplementary Information:**

The online version contains supplementary material available at 10.1186/s13018-023-04101-z.

## Introduction

Total knee arthroplasty (TKA) aims to restore knee pain and function, and improve the quality of life of patients [1–3] with end-stage osteoarthritis (OA) [4]. However, between 2 and 20% of patients who underwent TKA reported restricted motion and anterior knee pain [1, 5, 6]. These complications could arise from a non-optimal alignment of implant components [2, 7]. In this context, the introduction of robotic-assisted TKA is supposed to improve the accuracy of component positioning and to match more precisely patients’ anatomy and biomechanics [8]. Robotic TKA has been introduced to improve component alignment [9–11], impacting favourably on postoperative pain, hospitalisation, long-term implant survival [12, 13], and patient satisfaction [14]. However, the advantages of robotic surgery over conventional freehand TKA are still unclear, and high quality clinical investigations on large scale are necessary. Therefore, a single-blind randomised controlled trial will be conducted to evaluate TKA using the CORI robotic system (Smith & Nephew PLC, London, Great Britain). The primary outcome of interest is to compare robotic-assisted TKA versus the conventional freehand TKA in terms of patient-reported outcome measures (PROMs), length of hospitalisation, blood values, blood transfusion units, and range of motion. The second outcome of interest is to evaluate the accuracy of component positioning of robotic-assisted TKA compared to the conventional TKA.

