## Methods

### Study protocol

The present study shall be conducted in accordance with the SPIRIT 2013 statement (defining standard protocol items for clinical trials) [15]. All patients who will receive a TKA at the Department of Orthopaedic Surgery of the Eifelklinik St. Brigida in Simmerath (Germany) will be prospectively invited to participate in the present investigation. The recruitment will start on January 1, 2023, and will stop on January 1, 2033. The present study shall be conducted according to the principles of the Declaration of Helsinki. The shall authors receive no financial support for the research, authorship, and/or publication of this article. The protocol of the study has been prospectively registered and approved by the German Registry of Clinical Trials (ID DRKS00030614). Ethics approval has been received from the North Rhine Medical Council, Dusseldorf, Germany (ID 2022374).

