### Outcomes of interests

The primary outcome of interest is to compare robotic-assisted TKA using CORI robotic system versus conventional freehand arthroplasty. The surgical duration, length of the hospitalisation, blood analyses, implant positioning, blood units transfused, ROM, PROMs, and complications will be collected from both groups and compared as shown in Fig. 1.

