**Fig. 1 Fig1:**
[figure not shown]
Set up of follow-ups and data extraction

The second outcome of interest will be to compare implant positioning between robotic and conventional TKA. Implant positioning will be evaluated using anteroposterior plain radiographs of the leg using the software MediCAD Knie 2D (mediCAD Hectec GmbH, Altdorf, Germany), which is used to perform surgical planning of hip, knee, shoulder, trauma and spine surgery. The imaging references to assess implant positioning are shown in Fig. 2. An explanation of the main imaging references used is shown in Table 2.

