### Sample size evaluation

Assuming a true difference in means between the test and the reference group of 5 units, and a pooled standard deviation of 20 units, the study would require a sample size of 198 patients for each group (i.e. a total sample size of 396, assuming equal group sizes), to achieve a power of 80% and a level of significance of 5%, for declaring that the robotic TKA is superior to traditional TKA at 10 units margin of superiority, assuming a minimum clinically important difference for the WOMAC total subscale after TKA of 10 points [22].

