### Statistical analysis

All statistical analyses will be conducted by the main author (FM). For descriptive statistics, arithmetic mean and standard deviation shall be used. The unpaired t-test will be performed to assess baseline comparability, with values of *P* > 0.05 considered satisfactory. Data items will be collected by the assessors prospectively and entered into Microsoft Excel Spreadsheet Software version 2020 (Microsoft Corporation, Redmond, US). To compare robotic TKA versus freehand TKA, the IBM SPSS version 25 will be used. For continuous and binary data, the mean difference (MD) and odds ratio (OR) effect measures will be used. Standard error and 95% of confidence interval will be also evaluated. The null hypothesis will be that no difference between the two techniques exists. Both *χ*^2^ and unpaired *t*-test will be performed to evaluate whether the null hypothesis can be refused. Values of *P* < 0.05 were considered statistically significant. To evaluate the accuracy of implant positioning of robotic versus conventional TKA with regards to the pre-operative planning the standard deviation from the optimal implant alignment according to the patient anatomy will be evaluated using the IBM SPSS version 25.

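### The protocol does not fix one primary endpoint: five outcome groups are called primary, the sample size uses WOMAC total only, and no primary time point is given

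*Protocol article*

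**What the plan says.** The protocol article describes the primary outcome in two places, and the descriptions differ.

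- **Introduction.** The primary outcome is a comparison of the two techniques "in terms of patient-reported outcome measures (PROMs), length of hospitalisation, blood values, blood transfusion units, and range of motion". That is five groups of outcomes. Accuracy of component positioning is given as the second outcome.
- **Methods, Outcomes of interests.** "The primary outcome of interest is to compare robotic-assisted TKA using CORI robotic system versus conventional freehand arthroplasty". This sentence names no variable. The next one does: "The surgical duration, length of the hospitalisation, blood analyses, implant positioning, blood units transfused, ROM, PROMs, and complications will be collected from both groups". That is eight items. Compared with the Introduction it adds surgical duration, implant positioning and complications.
- **Same section, after Figure 1.** "The second outcome of interest will be to compare implant positioning between robotic and conventional TKA". Implant positioning is therefore in the list that follows the primary-outcome sentence and is also the second outcome.
- **Sample size evaluation.** The calculation uses one measure, "assuming a minimum clinically important difference for the WOMAC total subscale after TKA of 10 points". No time of assessment is attached to it.
- **Randomisation and blinding; Data to be collected.** Follow-up is at 6 weeks, 12 months and every 24 months. ROM and blood values are also taken on set postoperative days. None of these times is marked as primary.
- **Statistical analysis.** There is one general null hypothesis of no difference between techniques, tested by t-test and chi-square. P values below "0.05 were considered statistically significant". No order of testing or split of the 5% is given.
- **Study protocol.** "The recruitment will start on January 1, 2023, and will stop on January 1, 2033". The target of 396 is not mentioned there.

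**The concern.** A primary endpoint is one variable at one time, and the trial's error rate and power are stated for it. Here the label covers five groups, and the one measure that was used for sizing is never called primary.

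As written, a significant difference in length of stay or in an early haemoglobin value could be reported as a positive primary outcome just as well as a difference in WOMAC. The 5% level and 80% power quoted with the sample size do not describe that procedure. Because no follow-up is singled out, the choice among 6 weeks, 12 months and later visits could also be made after the data are seen. The trial's headline conclusion depends on these choices.

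**Working it through.** **1. The plan's own sample size.** Inputs from Sample size evaluation: difference 5, SD 20, 80% power, 5% level (sidedness not stated), equal groups.

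n per group = 2 × (z_alpha + z_power)² × SD² / difference²

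- One-sided 5%: 2 × (1.645 + 0.842)² × 400 / 25 = 197.8, so **198**. This is the stated figure.
- Two-sided 5%: 2 × (1.960 + 0.842)² × 400 / 25 = 251.2, so **252**. This is not the stated figure.

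Taking the distance between the assumed difference of 5 and the stated 10-unit margin also gives 198, because |5 − 10| = 5. That margin does not fit the no-difference null in the analysis section, but this is a separate matter.

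Power with 198 per group and a two-sided 5% test: the standard error is 20 × √(2/198) = 2.010, and 5 / 2.010 = 2.487. Then Φ(2.487 − 1.960) = **70.1%**.

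So the stated number covers one comparison of one variable, one-sided.

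**2. False-positive chance if any one of the five groups may carry the claim.** The Introduction gives k = 5, and the Statistical analysis section gives 0.05 per test.

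Independent tests: 1 − 0.95⁵ = **22.6%**.

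The outcomes will be correlated, and the document gives no correlations. Five equally correlated two-sided z-tests were simulated (200,000 draws) over an assumed range:

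| Assumed correlation | At least one P < 0.05 among 5 |
|---|---|
| 0 | 22.6% |
| 0.3 | 20.8% |
| 0.5 | 18.3% |
| 0.7 | 14.9% |

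These figures count false positives in either direction. For false positives in favour of robotic TKA only, two-sided independent tests give 1 − 0.975⁵ = 11.9%. With one-sided 5% tests, the level at which the sample size reproduces, the figure is again 22.6%.

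**3. The five groups are not five variables.** Data to be collected lists three blood values on two postoperative days, ROM on five postoperative days and at each follow-up, and four patient-reported instruments. One possible count to the first 24-month visit is 4 × 3 for the instruments, 3 × 2 for blood, 5 + 3 for ROM, and 1 each for stay and transfusion: 12 + 6 + 8 + 1 + 1 = 28. If each were tested separately, the chance would be 1 − 0.95²⁸ = 76.2% with independence, and 64.1% to 32.9% at correlations of 0.3 to 0.7. The count is an assumption. It shows the direction only.

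**4. Splitting the 5% instead.** With five co-primary outcomes at 0.01 each, two-sided, and the plan's difference and SD used for illustration, 2 × (2.576 + 0.842)² × 400 / 25 gives 374 per group. With 198 per group, power is 46.5%. Keeping all five as primary is therefore not a cheap alternative.

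**The case against.** **Multiplicity and repeated measures are commonly left to an analysis plan, which is not shown.** This is true, and the absence of an adjustment method is not the fault here. The fault is in what the protocol does state: a primary outcome defined twice and differently, and a sample size tied to a measure that is not declared primary. An analysis plan could settle this only by overriding the protocol.

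**The article gives no rule that any one significant result wins.** This also stands. If all five groups had to succeed, the false-positive chance would not be inflated, although power would fall. The 23% is conditional on the any-one reading, which the text permits but does not state.

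A reader might go further in three ways that the document does not support.

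- *There are eight primary outcomes.* The eight items follow the primary-outcome sentence, but the article says only that they will be collected and compared. Only the five groups in the Introduction are tied to the word primary.
- *Every outcome is tested at every visit, so a false positive is more likely than not.* The analysis section names tests and a threshold. It does not say that each visit or each questionnaire item has its own test. Any high figure of that kind rests on a count made by the reader and, at its highest, on independence, which is implausible for haemoglobin with haematocrit or for ROM on consecutive days.
- *The 2033 end date leaves the analysis date open to choice.* A required number and a latest recruitment date can coexist. The roughly 2000 TKAs a year on site are counted before consent, the exclusion criteria and the learning-curve restriction. What stands is that the article does not say how 396 and 2033 relate.

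**Conclusion.** The concern holds in this form: the protocol does not fix a single primary endpoint or a primary time point, and its sections disagree on what is primary. If any of the five groups named in the Introduction may support the primary claim at 0.05, the chance of at least one false positive is about 23% with independence and about 15% to 21% at assumed correlations of 0.7 to 0.3. This is roughly three to four and a half times the nominal 5%. It is higher if components and visits are tested separately, by an amount that the document does not allow one to fix. The stated 5% and 80% apply to one WOMAC comparison only, and only to a one-sided test. The wording should be corrected before any outcome data are compared between the groups.

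**What to change.** 1. Name WOMAC total, the measure used for sizing, at one follow-up already in the schedule as the single primary endpoint. Twelve months is an example. The document does not itself favour one visit, so the investigators should choose and justify it.
2. Make all other outcomes secondary, including implant positioning, and report them as estimates with 95% confidence intervals without confirmatory claims.
3. Align the Introduction, Outcomes of interests, Sample size evaluation, Statistical analysis and the registry entry with that definition.
4. State the sidedness of the primary test. If it is two-sided, either restate power with 198 per group as about 70%, or recalculate: the plan's difference and SD need 252 per group, 504 in total.
5. Say whether recruitment ends at the target number, on 1 January 2033, or at whichever comes first.

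**Cost.** Items 1 to 3 and 5 need changes of wording and a registry update. Item 4 costs either a lower stated power or 108 more patients (504 − 396). The main downside is that a significant result on an outcome other than WOMAC can no longer be claimed as the primary result.

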## Methods

### Study protocol

The present study shall be conducted in accordance with the SPIRIT 2013 statement (defining standard protocol items for clinical trials) [15]. All patients who will receive a TKA at the Department of Orthopaedic Surgery of the Eifelklinik St. Brigida in Simmerath (Germany) will be prospectively invited to participate in the present investigation. The recruitment will start on January 1, 2023, and will stop on January 1, 2033. The present study shall be conducted according to the principles of the Declaration of Helsinki. The shall authors receive no financial support for the research, authorship, and/or publication of this article. The protocol of the study has been prospectively registered and approved by the German Registry of Clinical Trials (ID DRKS00030614). Ethics approval has been received from the North Rhine Medical Council, Dusseldorf, Germany (ID 2022374).

### Participants

Patients who will agree to participate in the present study will be informed preoperatively of the purpose of the study and shall sign a written informed consent to confirm their willingness to participate in the trial. The institution where the surgeries are conducted is accredited by “Endocert” (EndoCert certificate, Centres of German Endoprosthetic, German Society for Orthopedics and Traumatology), which supervises and certifies the quality of the surgical procedures. The enrolment in the study will not impact or change the standards used in the management of the patients at our institution.

### Randomisation and blinding

The present study is a protocol for a single-blind randomised controlled trial in which each group of participants is exposed to only one of the study interventions. Patients will be randomly allocated to robotic-assisted TKA or to conventional freehand TKA. All patients in whom a TKA is indicated will be sequentially allocated in a 1:1 ratio to surgeons who perform robotic-assisted TKA or to those who perform conventional freehand TKA at the time of their outpatient appointment. All patients, irrespective of their allocation, will follow the same clinical, imaging, and anaesthesiologic pre- and post-surgical pathways. Patients will be blinded to the allocation until the first postoperative days. Surgeons and personnel involved in the clinical management of the patients will be unblinded to the allocation. Data curacy and collection will be conducted by two assessors blinded to group allocation and not involved in the clinical management of the patients. Assessors will retrieve patient data at the following follow-up times: admission, perioperatively (from access to discharge), at 6 weeks, 12 months, and every 24 months postoperatively. Data from patients will be collected once the learning curve has been reached.

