### Eligibility criteria

The inclusion criteria are: (1) age above 18, (2) ability to consent, (3) symptomatic knee osteoarthritis stage II to IV according to the Kellgren-Lawrence classification [16] (Table 1). The exclusion criteria are: (1) acute or chronic inflammatory diseases, (2) neoplastic diseases, (3) pregnancy and lactation, (4) uncontrolled coagulopathy, (5) abnormal cell count, (6) severe peripheral neuropathy, (7) vascular diseases, (8) peripheral ulcers, (9) other condition that could influence the results of the present study.

**Table 1 Tab1:** Kellgren Lawarence classification

Stadium	Grade of OA	Description
0	No evidence of OA	No radiologic evidence of OA
I	Minimal OA	Doubtful narrowing of joint space and possible osteophytic lipping
II	Mild OA	Definite osteophytes and possible narrowing of joint space
III	Moderate OA	Moderate multiple osteophytes, definite narrowing of joint space, some sclerosis, and possible deformity of bone ends
IV	Severe OA	Large osteophytes, marked narrowing of joint space, severe sclerosis, and definite deformity of bone ends

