### Data to be collected

On admission, the demographic information (age at surgery, BMI, sex), stage of OA according to the Kellgren-Lawrence classification [16], PROMs, and blood values of each patient will be collected on admission. Concerning the blood values, the haematocrit, haemoglobin, and C-reactive protein (CRP) will be collected preoperatively, on the first and fifth postoperative days. The blood tests will be conducted on admission, postoperative day (POD) 1 and 5 by dedicated healthcare personnel. To assess ROM, the neutral-zero method shall be used [17], using a standard baseline plastic 360-degree plastic pocket goniometer with flexion-hyper extension gauge (ProHealthcareProducts.com, Park City, US). ROM surgery will be assessed by moving the foot from a neutral starting position (neutral position in extension) in flexion and extension. ROM data will be collected on admission, on POD 1, 2, 3, 4, 5, and at each follow-up appointment by medical personnel who has not performed the index surgery. The German version of the Western Ontario and McMaster Universities Osteoarthritis Index (WOMAC) [18] and the visual analogue rating scale of health-related quality of life [19] will be used to rate the clinical outcomes. The patients will complete the questionnaires at admission and at each post-operative follow-up appointment. To evaluate the activity level of the patients included in the trial, the German version of the Tegner score will be administered [20]. In addition, a further seven questions Likert-like questionnaire shall be administered to all patients. This questionnaire is routinely used at our institution to rate the function of the knee in patients who undergo TKA. The questionnaire enquires about the activities related to the knee, post-operative overall patient satisfaction, patient satisfaction with the function of the knee, and information concerning walking distance. The Likert-like questionnaire is reported in Fig. 3, and the German version is available in Additional file 1.

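### Allocation covers every patient with a TKA indication and is not made conditional on consent and eligibility, so patients can be excluded or left unenrolled after the arm is known

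*Protocol article*

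**What the plan says.** All references are to the protocol article.

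- **Who is allocated, and when** (Randomisation and blinding): "All patients in whom a TKA is indicated will be sequentially allocated in a 1:1 ratio to surgeons who perform robotic-assisted TKA". The alternative is a surgeon who operates freehand, and the assignment is made when the patient attends the outpatient clinic. The population is defined by the indication for surgery. Neither consent nor eligibility is named as a condition.
- **Consent** (Participants): those who agree to take part "will be informed preoperatively of the purpose of the study" and sign a consent form. The text does not say whether this comes before or after allocation.
- **Eligibility** (Eligibility criteria): three inclusion and nine exclusion criteria. Two matter here: "5) abnormal cell count", with no sample, date or threshold, and "9) other condition that could influence the results of the present study", with no definition or decision-maker.
- **Blood tests** (Data to be collected): "The blood tests will be conducted on admission, postoperative day (POD) 1 and 5 by dedicated healthcare personnel". The values listed are haematocrit, haemoglobin and CRP.
- **Who knows the arm** (Randomisation and blinding): "Surgeons and personnel involved in the clinical management of the patients will be unblinded to the allocation". Patients are to remain blinded until the first postoperative days. "Data curacy and collection will be conducted by two assessors blinded to group allocation", but these assessors are not given the task of judging eligibility.

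**The concern.** Random allocation protects the comparison only if the decision to include a patient is made without knowledge of the arm. Here allocation is to a type of surgeon, so the surgeon knows the arm at once. If consent and some criteria are still open at that point, someone who knows the arm can decide whether the patient counts. Exclusion 9 is the easiest route, because it is worded by a condition's possible effect on the results and so invites a judgement about expected outcome.

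If such decisions differed between arms, the groups compared would no longer be the groups allocated. WOMAC, transfusion and length of stay would then carry a selection bias that a larger sample does not remove. The problem is separate from whether the sequence is predictable: it would remain with a perfect random list.

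**Working it through.** **Step 1. Order of events, section by section.**

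| Event | Time stated | Conditional on consent or eligibility? |
|---|---|---|
| Allocation to surgeon type | Outpatient appointment | No; every patient with a TKA indication |
| Consent | Before surgery | Not placed relative to allocation |
| Exclusion 5 (cell count) | Not stated | Sample not named; the only preoperative blood test described is at admission |
| Exclusion 9 (other condition) | Not stated | Open-ended; decision-maker not named |
| Surgeon and staff learn the arm | From allocation | – |

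Taken literally, the allocated population is wider than the eligible and consenting one. Some allocated patients must later be found ineligible or unwilling, and nothing requires that to be settled before the arm is known.

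**Step 2. The plan's own figure.** Inputs from Sample size evaluation: difference 5, SD 20, power 80%, significance level 5%, 198 per group.

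- One-sided 5%: n = 2 × (1.645 + 0.842)² × 20² / 5² ≈ 198 per group. This reproduces the stated figure.
- Two-sided 5%: the same formula with 1.960 gives 252, which does not.

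The sidedness is a separate matter. The figure of 198 is used below only for the standard error: SE = 20 × √(2/198) = 2.01.

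**Step 3. Illustration of size.** The document gives no exclusion rate and no prognosis for excluded patients, so both are assumptions. Let a share p more of one arm be removed, with those removed 10 WOMAC points worse than their arm's mean. The remaining patients' mean shifts by 10p/(1 − p). The two-sided type I error is P(Z > 1.96 − bias/SE) + P(Z < −1.96 − bias/SE), with 198 per arm in the SE.

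| p | Bias (points) | Share of the 5-point difference | Bias/SE | Two-sided type I error |
|---|---|---|---|---|
| 5% | 0.5/0.95 = 0.53 | 11% | 0.26 | 0.045 + 0.013 = 5.8% |
| 10% | 1.0/0.90 = 1.11 | 22% | 0.55 | 0.080 + 0.006 = 8.6% |

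**Step 4. A second model.** Remove the worst-prognosis share d from one arm only, with a correlation ρ of 0.3 to 0.5 between the prognosis judged and the outcome. Bias = 20 × ρ × φ(z)/(1 − d), where φ is the standard normal density and z its upper d quantile. The SE now allows for the smaller arm.

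| d | Bias (points) | Two-sided type I error |
|---|---|---|
| 2% | 0.30 to 0.49 | 5.2% to 5.7% |
| 5% | 0.65 to 1.09 | 6.2% to 8.3% |
| 10% | 1.17 to 1.95 | 8.8% to 15.7% |

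The two models agree in order of magnitude. At small differential exclusion the effect is slight. At 10% it is material against a planned difference of 5.

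**The case against.** Several objections are sound and limit the point.

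- **The cell count.** A reader might infer that exclusion 5 can be judged only on blood drawn at admission, after allocation. The document does not support that. The values listed for the admission sample do not include a cell count, the criterion names no sample, and an earlier result could be used.
- **Eligibility unknowable at allocation.** This is also too strong. Age, ability to consent, Kellgren-Lawrence stage and the history-based exclusions can be judged at the outpatient appointment.
- **Unblinded staff exclude patients.** The document does not say so. It says that clinical staff know the arm, but not who applies the criteria.
- **Consent.** Patients are to be blinded, so their own decision is planned without knowledge of the arm. Influence from those who invite them remains possible, which is a weaker claim.
- **Convention.** A catch-all exclusion is common, criteria ordinarily govern entry, and an article may leave the exact sequence to the full protocol.
- **Size.** The exclusion rates are assumed. A 10% difference between arms from these routes would be large.

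The argument from condensation does not dispose of the point. The article is not silent: it states which patients are allocated and when, and that statement does not fit its own eligibility and consent sections. The rule excluding patients for deviation (Surgical procedures and rehabilitation protocol) is a different issue, though it shows that the plan accepts removal after allocation.

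**Conclusion.** The point holds in a limited form. As written, allocation applies to all patients with a TKA indication at the outpatient appointment and is not conditional on consent or confirmed eligibility. With an open-ended exclusion, a laboratory criterion without a named sample, and clinical staff who know the arm, the text permits arm-aware exclusion or non-enrolment of patients already allocated. It does not show that this will occur.

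No bias can be estimated from the document. Under the simple illustration it is about 0.5 to 1.1 WOMAC points, with a two-sided type I error of about 5.8% to 8.6%, at 5% to 10% differential removal. Those figures rest wholly on the assumed rates and the assumed 10-point deficit. The case for a change is that the safeguard is cheap and the bias, if it arose, could not be corrected by sample size.

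**What to change.** 1. In Randomisation and blinding, replace the population defined by TKA indication with patients who have signed consent and whose eligibility criteria have all been confirmed and recorded before allocation.
2. For exclusion 5, name the blood count to be used and require that it be available before allocation. Keep the admission draw as the baseline for the blood outcomes.
3. Reword exclusion 9 as a condition judged and recorded before allocation, and remove the reference to the results.
4. State that the criteria close at allocation, and that a patient with a later finding has it recorded and is analysed in the allocated group.

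The cost is mainly protocol wording, plus making sure that a blood count is on file by the time of allocation. The downside is that a few patients with late findings remain in the analysis. Recruitment is planned to run to January 1, 2033, so an amendment would protect future enrolment.
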